### Statistical Analysis

The primary objective of this study is to determine whether PRISM, along with usual care, reduces functional disability more than usual care alone. The primary outcome or measure of efficacy is the FDI score at 3 months postrandomization (control group) or postintervention. The secondary efficacy outcomes are patient psychological distress (as measured with the K6), as well as the patient-reported pain intensity (as measured with the PROMIS Pediatric Numeric Rating Scale v1.0 – Pain Intensity). The secondary objectives are to determine a reduction in pain intensity and psychological distress with PRISM at intervention completion; determine reductions in functional disability, pain intensity, and psychological distress with PRISM at 6 months postintervention; evaluate potential patient- and caregiver-level moderators of PRISM; examine implementation outcomes (feasibility, acceptability, appropriateness); and identify facilitators of and barriers to engagement in PRISM.

The study team plans to publish the study findings in a peer-reviewed pediatrics, psychology, or rheumatology journal to disseminate the findings. No individually identifiable protected health information will be published. Summary results will be available on ClinicalTrials.gov.

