Furthermore, we will explore adolescent- and caregiver-level moderators of intervention effects, guided by an intersectionality framework [59]. For instance, we will investigate whether age moderates the intervention’s impact on functional disability by including the age × intervention interaction in the linear mixed effects regression model. If the interaction is significant, we will interpret it by plotting simple regression lines for younger (12-14 years) and older (15-16 years) adolescents. If PRISM proves more beneficial for younger participants, future studies may focus on this age group to maximize intervention effects. Additionally, we will evaluate whether biological sex moderates the intervention’s impact, ensuring adequate inclusion of male participants, given the predominance of females in the population with CMP [60].

Analyses will include calculation of eligibility, recruitment and attrition rates, and power considerations for the future full-scale RCT and evaluation of treatment fidelity. We will report the number of eligible subjects approached, the proportion of those subjects enrolled in the study, and the mean percentage of required sessions (PRISM 1-4 sessions + “coming together” session) attended among enrolled subjects. The study will be defined as feasible (binary) if the recruitment rate is ≥60%, the completion rate of all sessions among enrolled subjects is ≥70%, and the mean FIM score is ≥4. The intervention will be acceptable and appropriate if the mean AIM and IAM scores are ≥4 each. Intervention satisfaction (including session-specific and overall intervention satisfaction) will be reported as mean scores from the 5-point Likert scale (1=very dissatisfied to 5=very satisfied).

With a sample of 130 patient participants and an assumed ~20% attrition rate, we have more than 80% statistical power to detect a difference down to 5 points in the FDI between the intervention and control arms, given a prespecified mean FDI score of 26.9 (SD 11.8) and a significance level of .05 for the Student *t*-test. Table 1 lists the detectable differences (DDs) for the outcomes of interest, as well as the minimal clinically important difference (MCID) for each measure. The effect sizes of CBT on the FDI in similar patient populations have been strong to moderate (0.8-0.9), with between-group differences in the FDI score of 5.39 (95% CI 1.57-9.22). Therefore, we will be adequately powered for the primary outcome [61,62].

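### Interpreting the age × intervention interaction only when it is significant, and then letting it steer the next trial, would pass on selectively inflated estimates: a cheap wording improvement

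*Protocol article*

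**What the plan says.** The Statistical Analysis section of the protocol article lists, among the secondary objectives, to "evaluate potential patient- and caregiver-level moderators of PRISM". The Quantitative Data section describes this work as exploratory and gives age as the worked example. An age × intervention term goes into the linear mixed effects model, and then: "If the interaction is significant, we will interpret it by plotting simple regression lines for younger (12-14 years) and older (15-16 years) adolescents". The next sentence gives a use for the result: "If PRISM proves more beneficial for younger participants, future studies may focus on this age group to maximize intervention effects". Sex is named as a second moderator, with no rule of this kind attached.

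The power statement in the same section concerns the comparison of the two arms: "we have more than 80% statistical power to detect a difference down to 5 points in the FDI between the intervention and control arms". Table 1 likewise gives detectable differences between arms only. No detectable size is given for an interaction, and nothing is said about how an imprecise one should be read.

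**The concern.** The pilot's stated purpose includes obtaining the data needed to plan a larger trial, so its moderator results are meant to be carried forward. A rule that ties interpretation to significance selects what is carried forward. When the test has low power, this selection errs in two ways. A real difference in effect by age will usually miss the threshold and so fall outside the stated interpretation. An estimate that does pass must be large, and will on average be larger than the truth. If such an estimate then shaped the age range of the next trial, that trial could leave out older adolescents because of an inflated or chance result.

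**Working it through.** **Inputs.** 100 evaluable patients (Quantitative Data; Table 1), 1:1 allocation (Recruitment and Randomization), FDI SD 11.8 and significance level .05 (Quantitative Data). The article does not say one- or two-sided; two-sided is assumed. The reference sizes are 5 points (the stated detectable between-arm difference) and 8 points (the MCID in Table 1). The article gives no expected interaction size, so both are illustrations.

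**The plan's own figure.** For the between-arm difference, SE = 11.8 × √(1/50 + 1/50) = 2.36. Then 5/2.36 = 2.12, and two-sided power is about 56%, not above 80%. With all 65 per arm it is about 68%. The detectable difference at 80% power with 50 per arm is about 6.6 points. The stated figure is therefore not reproduced. That is a separate matter, and the steps below use only the sample size and SD.

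**Interaction, simplest case.** Two equal age groups split evenly by arm give four cells of 25. The interaction is a difference of two differences:

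SE = 11.8 × √(4/50 + 4/50) = 11.8 × 0.4 = 4.72, twice the between-arm SE.

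- Smallest significant estimate: 1.96 × 4.72 = 9.25 points.
- Detectable with 80% power: (1.96 + 0.84) × 4.72 ≈ 13.2 points.
- Power at 5 points: 5/4.72 = 1.06; Φ(1.06 − 1.96) plus a negligible opposite tail = 18.5%.
- Power at 8 points: 8/4.72 = 1.69; Φ(1.69 − 1.96) = 39.6%.

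**Exaggeration among significant estimates.** The mean of a normal estimate, given that it exceeds 9.25, is d + SE × φ(z)/(1 − Φ(z)), with z = (9.25 − d)/SE.

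- d = 5: z = 0.90; 5 + 4.72 × 1.45 = 11.8; 11.8/5 ≈ 2.4-fold.
- d = 8: z = 0.265; 8 + 4.72 × 0.97 = 12.6; 12.6/8 ≈ 1.6-fold.

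Simulation of 1,000,000 estimates gave the same ratios.

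**Closer to the planned model.** Baseline adjustment multiplies the SE by √(1 − ρ²), with ρ assumed. For continuous age, a uniform spread over 12 to under 17 years is assumed, with SD 5/√12 = 1.44 years. The interaction is expressed over 2.5 years, the distance between the mean ages of the two plotted groups (13.5 and 16). Unadjusted, the SE is 2.5 × 2 × 11.8/(√100 × 1.44) ≈ 4.09.

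| Setting | SE | Smallest significant estimate | Power at 5 | Power at 8 |
|---|---|---|---|---|
| Equal groups, unadjusted | 4.72 | 9.25 | 18.5% | 39.6% |
| 60/40 groups, unadjusted | 4.82 | 9.44 | 18.0% | 38.3% |
| Equal groups, all 130 patients | 4.14 | 8.11 | 22.7% | 48.9% |
| Equal groups, ρ = 0.7 | 3.37 | 6.61 | 31.7% | 66.0% |
| Continuous age, unadjusted | 4.09 | 8.01 | 23.1% | 49.9% |
| Continuous age, ρ = 0.7 | 2.92 | 5.72 | 40.3% | 78.2% |

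In every row the smallest significant estimate is above 5 points, so any significant result overstates a true 5-point interaction. With equal groups and ρ = 0.7 the average exaggeration is about 1.8-fold at 5 points and 1.2-fold at 8.

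**The case against.** The strongest reply is that the text is milder than the concern suggests, and much of this stands.

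- **Reporting.** A reader might infer that non-significant interactions will go unreported or be taken as no moderation. The article does not say so. It makes a follow-up plot and its interpretation conditional on significance, for age only. No such rule is stated for sex or for caregiver factors.
- **The next trial.** A reader might infer that the next trial will be restricted by age. The article says only that future studies may have this focus, and its Conclusion describes the planned multicenter trial as one for adolescents with CMP, without a narrower age range.
- **Number of tests.** A reader might add a large false-positive risk across many moderators. Only age and sex are named. Two independent tests at 5% give 1 − 0.95² = 9.75%; any larger count would be a guess, and handling multiplicity is commonly left to the SAP.
- **Males.** A reader might object that nothing backs the phrase "ensuring adequate inclusion of male participants". A condensed article may leave recruitment targets to the full protocol, so their absence here shows nothing. No male share is given either, so no precision figure for the sex interaction can be drawn from the document.
- **The model.** The simple calculation is not the planned analysis. Continuous age, covariates and repeated measures would all help, and at 8 points the most favourable row above reaches 78%. Low power for interactions is also usual in a trial of this size, and the article claims adequate power only for the primary outcome.

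None of this removes the significance condition or the sentence that follows it. Both are in the text, and calling the analysis exploratory is a reason to report estimates with intervals rather than to filter them by p value.

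**Conclusion.** The point holds in a limited form. For age, the article makes interpretation depend on significance and names a possible consequence for future studies. On its sample size and SD, with equal unadjusted age groups, the test has about 18% power at 5 points and 40% at 8. Estimates that pass are inflated about 2.4-fold and 1.6-fold on average. Under more favourable assumptions power at 5 points rises to about 40%, which is still low.

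These figures rest on assumed interaction sizes, an assumed age distribution, an assumed baseline correlation and a two-sided test. A true interaction well above 8 points would be less affected. The documents do not support the stronger conclusion that the definitive trial will be wrongly narrowed, or that any moderator finding must be grossly wrong. Severity is low, because the analysis is exploratory, the primary result is untouched and the narrowing is only a possibility.

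**What to change.** Replace the significance condition with a statement such as: *For age, sex and any other moderator examined, the interaction coefficient and its 95% confidence interval will be reported whatever the p value, and read as hypothesis-generating.* The age-specific lines can then be plotted in all cases.

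Change the sentence on focusing future studies so that it says age will be considered as a stratification factor in the next trial, not as a ground for restricting entry on the strength of this result.

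This is a cheap improvement: two sentences and one table of estimates, with no new data. The downside is that the moderator conclusions become more cautious.

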**Methods:**

The Resilience Coaching for Adolescents with Chronic Musculoskeletal Pain pilot study is an investigator initiated, 2-arm, randomized controlled trial (RCT) of PRISM in the interdisciplinary management of CMP among adolescents. The study will compare usual care versus PRISM+usual care among adolescents newly diagnosed with CMP in the outpatient setting. One caregiver per patient will also be enrolled. The control group will receive usual care with no specific intervention. The treatment arm will receive PRISM, which is a remotely delivered, 1-on-1resilience coaching program, consisting of 4 required skill-based sessions and an optional final session. Sessions will be delivered every 1-2 weeks, lasting about 3 months in total. The primary outcome is the Functional Disability Inventory (FDI) score at 3 months postrandomization. The secondary objectives are to evaluate potential patient- and caregiver-level moderators of PRISM and identify facilitators of and barriers to engagement in PRISM. The estimated sample size is 65 patient-caregiver dyads per group, for a total of 130 dyads.

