### The PRISM Intervention

PRISM consists of 4 required skill-based sessions that focus on stress management, goal setting, cognitive restructuring, and benefit finding (see Figure 1). The optional fifth “coming together” session focuses on discussing with a family member, with the participant’s permission, the skills that the participant found beneficial, the ones they did not, and how they can continue to implement the skills learned in the future once the program finishes. Each session is around 30-50 minutes, with sessions scheduled 1-2 weeks apart. Participants are given access to “cheat sheets” and worksheets for each session and a mobile app that can be used to practice the skills learned.

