**Figure 2 figure2:**
[figure not shown]
PRISM RCT recruitment, screening, and consent process. CHOP: Children’s Hospital of Philadelphia; CMP: chronic musculoskeletal pain; e-consent: electronic consent; EMR: electronic medical record; PRISM: Promoting Resilience in Stress Management; PROMIS: Patient-Reported Outcomes Measurement Information System; RCT: randomized controlled trial.

Those who are not approached at their clinic visit can be contacted retroactively via telephone and, if interested and eligible, can be e-consented via REDCap (Research Electronic Data Capture), a secure, web-based software platform designed to support data capture for research studies [24,25]. For anyone who declines participation, their reasoning is recorded in the study’s master log. Study personnel attempt to contact patient-caregiver dyads a maximum of 3 times before discontinuing recruitment efforts. Once baseline surveys are complete, the dyads will be randomly assigned to a study arm using a 1:1 allocation ratio: PRISM+usual care versus usual care.

Stratified randomization will be implemented by the study statistician in REDCap to ensure a balance in sex (male vs female) and clinic (rheumatology clinic vs interdisciplinary pain [amplified musculoskeletal pain] clinic) between the 2 study arms. The final randomization scheme will be prepared by a statistician independent of the study team to prevent bias. Study staff will not get access to randomization algorithms. Tracking of dyads and randomization will be recorded in the study’s master log.

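### The binary feasibility criterion is inconsistent on the session count and unclear on denominator and metric, so the same attendance data can pass or fail it

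*Protocol article*

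**What the plan says.** The Quantitative Data section of the protocol article makes feasibility a yes/no outcome with three joint conditions: a recruitment rate of at least 60%, a mean Feasibility of Intervention Measure (FIM) score of at least 4, and a session condition, namely that "the completion rate of all sessions among enrolled subjects is ≥70"%.

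The sentence just before it says that the study will report "the mean percentage of required sessions (PRISM 1-4 sessions + “coming together” session) attended among enrolled subjects". The same sentence uses the word enrolled for entry to the trial as a whole: "the proportion of those subjects enrolled in the study".

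Elsewhere the session count differs:

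- Abstract, Methods: a programme "consisting of 4 required skill-based sessions and an optional final session".
- The PRISM Intervention: "PRISM consists of 4 required skill-based sessions", followed by "The optional fifth “coming together” session focuses on discussing with a family member".
- Introduction: PRISM is described as having 5 skill-based sessions, with no required/optional distinction.

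On who is enrolled, Recruitment and Randomization places consent and baseline surveys first, after which "the dyads will be randomly assigned to a study arm using a 1:1 allocation ratio". The Control Group section states that controls do not receive PRISM.

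**The concern.** A prespecified yes/no criterion should give one answer for one set of data. This one leaves three choices open: which sessions count, who is in the denominator, and whether the quantity is a proportion of people or an average of sessions. On the first, the article contradicts itself. On the second, the literal wording brings in participants who have no sessions to attend.

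The three feasibility conditions are joined by *and*, so failing the session condition makes the whole verdict not feasible. The Abstract puts feasibility first in the study's main goal and says the pilot will inform a larger multisite trial. If the definition is settled only after attendance is known, the verdict is no longer prespecified.

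**Working it through.** The 70% is a chosen cut-off, not a derived figure, so there is nothing to reproduce. The check is what the criterion returns under each reading.

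**Inputs from the article.** 65 dyads per arm, 130 in total (Abstract); 1:1 allocation (Recruitment and Randomization); no PRISM sessions for controls (Control Group); four required sessions plus one optional (Abstract; The PRISM Intervention) or five required (Quantitative Data); attrition of ~20% and threshold of 70% (Quantitative Data).

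**Assumptions.** The attrition figure concerns evaluable subjects, not session attendance. For illustration, it is treated here as the share of the PRISM arm attending no session, with everyone else completing sessions 1-4. The article gives no figure for uptake of the fifth session.

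**Step 1: literal denominator.** With all enrolled patients in the denominator and perfect attendance in the PRISM arm, the maximum is 65/130 = 50%. Counting enrolled caregivers as well gives 65/260 = 25%. Neither reaches 70%.

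**Step 2: PRISM-arm denominator (65), 20% attrition.** Completers of sessions 1-4: 0.80 × 65 = 52.

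- Share completing sessions 1-4: 52/65 = 80%. Pass. The minimum is 46 of 65, since 0.70 × 65 = 45.5.
- Mean percentage of five sessions, no optional uptake: 0.80 × 4/5 = 64%. Fail. With zero uptake, passing needs 0.70/0.80 = 87.5% of the arm attending four sessions, that is 57 of 65.
- Share completing all five: passes only if uptake of the fifth session among those who finish the first four is at least 0.70/0.80 = 87.5%. In whole participants this is 46 of 52.

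**Step 3: range over the attrition assumption.** Let *c* be the share of the PRISM arm completing sessions 1-4, with the rest attending none.

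| *c* | Sessions 1-4 completed (*c*) | Mean of five sessions, no optional uptake (*c* × 4/5) | Uptake of fifth session needed for all-five completion ≥70% (0.70/*c*) |
|---|---|---|---|
| 100% | 100%, pass | 80%, pass | 70% |
| 90% | 90%, pass | 72%, pass | 77.8% |
| 80% | 80%, pass | 64%, fail | 87.5% |
| 70% | 70%, pass | 56%, fail | 100% |

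The readings disagree across much of this range. Even at *c* = 100%, all-five completion is 0% if nobody takes the optional session, while the mean-attendance reading gives 80%.

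**The case against.** The strongest reply is that the intended meaning is easy to guess. Controls have no sessions to complete, and the same sentence uses the FIM score, which rates an intervention and so points to PRISM recipients. A reader who infers from the 50% cap that the threshold cannot be met is therefore going too far: the cap belongs to the literal wording, and 70% is attainable in the PRISM arm. This stands.

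A reader might also infer that the rule would fail a programme delivered exactly as designed. The article does not support that as a general statement. It holds if completion means finishing all five sessions and fewer than 70% of the arm do so. It does not hold if the metric is the mean percentage named in the preceding sentence, because four of five sessions for everyone gives 80%. Nor is it certain that the two sentences intend different metrics; the text leaves this open.

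Two further points are fair. The Statistical Analysis section lists implementation outcomes under the secondary objectives, and nothing makes the multicentre trial conditional on this label. Attendance will be recorded in any case and could be reported under several definitions.

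It might also be said that a condensed article may leave such detail to the full protocol. That does not answer the point. The article states the threshold, the denominator and the list of required sessions, and these conflict with its own description of the programme. Reporting several definitions afterwards also does not say which one decides a binary verdict.

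**Conclusion.** The concern holds as an internal inconsistency with a practical consequence. The contradiction over the fifth session is plain in the text and needs no assumption. The denominator is wrong as literally written (cap 50%), although the PRISM arm was probably meant. The metric is ambiguous.

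With the PRISM arm as denominator, 70% can be reached, so the criterion is not impossible. The verdict nevertheless turns on the reading: in the 20% illustration it runs from a clear pass to a fail, and the all-five reading depends on an uptake figure the article does not give. These sizes rest on the stated attendance assumptions and show sensitivity; they do not predict failure.

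Severity: should-fix. The primary FDI analysis is unaffected.

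**What to change.** Before attendance data are reviewed:

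1. Reconcile the Abstract, the Introduction, The PRISM Intervention and Quantitative Data on how many sessions there are and which are required.
2. Restate the completion criterion with adolescents randomized to PRISM as the denominator.
3. Name one metric: either the share of participants completing the counted sessions or the mean percentage attended.

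If the fifth session is confirmed as optional, as the Abstract and The PRISM Intervention state, the criterion becomes: at least 70% of adolescents randomized to PRISM complete sessions 1-4. The fifth session then leaves the list of required sessions, and mean attendance and optional-session uptake are reported separately as descriptive measures.

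The cost is a change to one paragraph, plus aligning the session count elsewhere. No additional data are needed.

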#### Quantitative Data

Quantitative measures will be used to assess the primary and secondary efficacy outcomes, moderators of PRISM, and implementation outcomes. Demographics and baseline clinical characteristics will be summarized by standard descriptive summaries (eg, means and SDs for continuous variables, such as age, and percentages for categorical variables, such as gender). The primary analysis will use an intention-to-treat (ITT) approach to mitigate confounding from nonrandom participant attrition. We anticipate a total of 100 evaluable subjects. To ensure valid randomization, we will assess demographic and clinical features, along with baseline measures of outcomes, such as physical function, pain intensity, and psychological distress, and compare the intervention to the control arm. The primary outcome will be functional disability (FDI score) assessed at the end of the intervention (month 3). The key predictor is PRISM. Secondary outcomes will include the FDI score at the conclusion of the observation period (month 9, 6 months postintervention) and psychological distress (K6 total) and pain intensity (PROMIS Pediatric Numeric Rating Scale v1.0 – Pain Intensity) at both 3 and 9 months.

Assuming balanced arms postrandomization, we will evaluate the differences in clinical outcomes between the 2 arms at months 3 and 9 using 2-sample Student *t* tests. Longitudinal changes from month 3 to month 9 will be assessed using MANOVA (multivariate analysis of variance) and linear mixed effects models to account for within-subject correlation due to repeated measures. The linear mixed effects model can additionally adjust for a few known prognostic covariates, such as fulfillment of criteria for juvenile FM. Similar analyses will examine outcomes of psychological distress and pain intensity separately.

Linear regression will be conducted to assess the association between the change in FDI scores and changes in the intervention targets, adjusted for baseline covariates of interest. These analyses will be repeated to examine correlations between changes in secondary outcomes (pain intensity and psychological distress) and hypothesized intervention targets at month 3, and we will conduct multivariable linear regression models, adjusting for covariates of interest.

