**Table 1 table1:** DDs^a^ in mean instrument scores between groups, given 80% power and a 5% type I error rate (N=100^b^).

Outcome (instrument)	Sample mean (SD)^c^	MCID^d^	DD
Physical function (FDI^e^)	26.9 (11.8)	8.0	5.0
Pain (PROMIS^f^ Pediatric Numeric Rating Scale v1.0 – Pain Intensity)	6.2 (2.3)	2.0	0.9
Psychological distress (K6^g^)	9.1 (6.0)	3.0^h^	2.4

^a^DD: detectable difference.

^b^Anticipated dropout rate of ~20% (total=130), resulting in 100 evaluable subjects.

^c^Sample means from preliminary data.

^d^MCID: minimal clinically important difference.

^e^FDI: Functional Disability Inventory.

^f^PROMIS: Patient-Reported Outcomes Measurement Information System.

^g^K6: Kessler-6 Psychological Distress Scale.

^h^Half the SD of mean baseline scores.

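### The claimed power above 80% for 5 FDI points, and all three detectable differences in Table 1, do not follow from the plan's own inputs; power for 5 points is about 56%

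*Protocol article*

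**What the plan says.** The power paragraph (protocol article, Statistical Analysis, Quantitative Data) takes 130 patients with attrition of roughly 20% and claims that "we have more than 80% statistical power to detect a difference down to 5 points in the FDI between the intervention and control arms". The other inputs it names are an FDI mean of 26.9 with SD 11.8, a .05 level and Student's t test. After citing a between-group FDI difference of 5.39 points from CBT studies, it concludes: "Therefore, we will be adequately powered for the primary outcome".

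Table 1 is headed as detectable differences "in mean instrument scores between groups, given 80% power and a 5% type I error rate", with N=100. Its rows are:

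| Outcome | SD | MCID | Detectable difference |
|---|---|---|---|
| FDI | 11.8 | 8.0 | 5.0 |
| Pain intensity | 2.3 | 2.0 | 0.9 |
| K6 | 6.0 | 3.0 | 2.4 |

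The 100 is a total. The Quantitative Data section says "We anticipate a total of 100 evaluable subjects", and footnote b of Table 1 says "Anticipated dropout rate of ~20% (total=130), resulting in 100 evaluable subjects". Under Recruitment and Randomization, dyads are "randomly assigned to a study arm using a 1:1 allocation ratio". That leaves 50 evaluable patients per arm. The planned comparison between arms at months 3 and 9 is an unadjusted two-sample Student t test, the same test that the power statement names.

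**The concern.** A 5-point difference with SD 11.8 is a standardized difference of 5/11.8 = 0.42. Fifty patients per arm is visibly too few to detect that with 80% power, so the claim needed checking.

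The sentence is the trial's justification of its size for the primary outcome. If it is wrong, readers will believe that a true 5-point effect would be missed less than 20% of the time when the real figure is about 45%, and they may give a null result more weight than it deserves. Table 1 also sets each detectable difference beside an MCID, and in every row the former is the smaller; an error there can reverse that comparison. Finally, the protocol intends the trial to inform power considerations for a full-scale RCT, so a mistake in method could carry over into that trial's size.

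**Working it through.** **Inputs.** 130 randomized and 100 evaluable in total (Quantitative Data; Table 1, footnote b); 1:1 allocation, so n = 50 per arm; SDs 11.8, 2.3 and 6.0 (Table 1); significance level .05; two-sample t test. The article does not say whether the test is one- or two-sided. I take two-sided and also try one-sided.

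**Formula.** For a true difference Δ, the t statistic has 2n − 2 degrees of freedom and noncentrality Δ / (SD·√(2/n)). Power is the probability that it falls beyond the critical value.

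**Primary outcome, n = 50.** The standard error is 11.8 × √(2/50) = 2.36. The noncentrality is 5/2.36 = 2.12, and the two-sided critical value on 98 degrees of freedom is 1.98. Power is **55.5%** (56.3% by the normal approximation). The stated figure of more than 80% is not reproduced.

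**Detectable differences.** With n = 50 per arm, 80% power needs a standardized difference of 0.566.

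| Outcome | Printed | Power at printed value | 80%-power difference, 50 per arm | Printed value too small by | MCID |
|---|---|---|---|---|---|
| FDI | 5.0 | 55.5% | 0.566 × 11.8 = 6.68 | 25% | 8.0 |
| Pain | 0.9 | 49.1% | 0.566 × 2.3 = 1.30 | 31% | 2.0 |
| K6 | 2.4 | 50.8% | 0.566 × 6.0 = 3.40 | 29% | 3.0 |

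The corrected K6 value exceeds its MCID; power at 3.0 K6 points is about 70%. The corrected FDI and pain values stay below theirs.

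**Other readings of the inputs (power for 5 FDI points).**

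| Reading | Two-sided .05 | One-sided .05 |
|---|---|---|
| 50 per arm | 55.5% | 67.7% |
| 52 per arm (130 × 0.8 = 104) | 57.2% | 69.2% |
| 65 per arm, no attrition | 66.9% | 77.6% |

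None reaches 80%.

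**Where the printed figures may come from.** With 100 *per arm*, two-sided, the 80%-power differences are 4.70, 0.92 and 2.39, and power for 5 FDI points is 84.7%. This matches the printed 0.9 and 2.4 after rounding and fits the phrase about more than 80% power. A one-sample calculation with n = 50 gives 4.77, 0.93 and 2.43, which is also close, but it is not the planned test.

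**Size needed for the printed differences.** 80% power with a two-sided t test needs 89 (FDI), 104 (pain) and 100 (K6) evaluable patients per arm. For the FDI that is 178 evaluable, or 178/0.8 = 222.5, so 223 randomized.

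**The supporting figures.** At the cited 5.39 points, power with 50 per arm and SD 11.8 is 61.8%. At the FDI MCID of 8.0 points it is 91.9%.

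**The case against.** The best defence is that the trial is adequately sized for the difference that matters. Power is about 92% at the plan's own FDI MCID of 8 points, and the corrected detectable difference of 6.7 is below that MCID. This stands, and it belongs beside the 56%. It does not save the text, because the adequacy sentence is drawn from the 5-point and 5.39-point figures and not from the MCID.

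A second defence is that this is a pilot whose definitive answer is left to a multisite trial. That softens the consequences. But the article makes efficacy on the FDI the primary objective and asserts adequate power for it, so the assertion should be true.

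A third is that adjusting for baseline could recover the power. To reproduce Table 1 with 50 per arm, the baseline-to-follow-up correlation would have to be about 0.66 (FDI), 0.72 (pain) and 0.71 (K6), from ρ = √(1 − (needed SD/stated SD)²) with needed SDs of 8.84, 1.59 and 4.24. The article states no such correlation and bases its power on the unadjusted t test.

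Two cautions on the criticism itself also stand. Entering the total of 100 as a per-arm number is a plausible cause but not a proven one, since another calculation comes close to the same figures. And although 5.39 points is 0.46 SD on this plan's SD, against the cited CBT effect sizes of 0.8 to 0.9, the cited studies may have had other SDs or used another kind of effect size. That comparison does not show the citation to be wrong. It shows only that 5.39 points does not support adequate power under this plan's SD.

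**Conclusion.** The power statement and Table 1 are wrong as written. With 50 evaluable patients per arm, the stated SDs, two-sided .05 and a two-sample t test, power for 5 FDI points is about 56%, and the differences detectable with 80% power are 6.7 (FDI), 1.3 (pain) and 3.4 (K6) in place of 5.0, 0.9 and 2.4. A true 5-point effect would be missed about 45% of the time.

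The only assumption beyond the document is the two-sided test, and a one-sided test does not change the conclusion. The gap between exact 20% attrition (104 evaluable) and the stated 100 (30/130 = 23% attrition) does not change it either. The error concerns the 5-point claim, the three table entries and the adequacy sentence that rests on them; it does not invalidate the design.

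**What to change.** 1. In the power paragraph, state about 56% power for 5 FDI points and an 80%-power difference of 6.7, for 50 evaluable per arm, and say that the test is two-sided.
2. In Table 1, replace the detectable differences by 6.7, 1.3 and 3.4, label N as 100 in total (50 per arm), and note that the K6 value exceeds its MCID of 3.0.
3. Delete the sentence on adequate power, or restate it as about 92% power at the FDI MCID of 8 points. If the 5.39-point figure is kept, give its power of about 62%.
4. If a baseline-adjusted primary analysis is adopted, give power under a stated baseline-to-follow-up correlation with its source. The 5-point claim needs about 0.66.

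The cost is wording in the protocol and, where it repeats these figures, the SAP. The stated figures become less favourable. No extra enrolment is proposed.
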